## Abstract

**Background:**

Living in residential aged care (RAC) facilities can be passivating and negatively impact residents’ well-being and quality of life. With a growing global population of older adults and an increasing number residing in RAC facilities, it is crucial to address these concerns. Person-centered reablement, which enhances activity and participation through tailored, multidisciplinary strategies, has shown promising results in home settings. However, its implementation in RAC facilities, especially in Sweden, requires further evaluation.

This research project will examine whether the reablement intervention in RAC (Re-RAC) impacts activity performance and satisfaction, participation, quality of life, and well-being, in older adults living in RAC facilities. Additionally, the project will evaluate the health-economic effects of the intervention and explore potential associations with the outcomes. A further aim is to describe the experiences of both the participating older adults and RAC facility staff involved in Re-RAC.

**Methods:**

This is a multi-center prospective pragmatic randomized controlled trial has two parallel groups comparing the Re-RAC intervention with usual care. A total of 86 participants are planned to be enrolled. The 8-week intervention will be evaluated using quantitative, qualitative, and health-economic methods. Data will be collected at baseline and after the intervention. Health-economic data will also be gathered 3 months before and after intervention. Primary outcomes are activity performance and satisfaction with performance captured using the Canadian Occupational Performance Measure; secondary outcomes, i.e., health-related quality of life, psychological well-being, and physical activity levels will also be evaluated. Experiences of participants and staff will be captured through individual and focus-group interviews. Cost-effectiveness will be estimated by calculating the cost per quality-adjusted life year gained.

Quantitative data will be analyzed using descriptive and comparative statistics; qualitative data will be analyzed using thematic analysis and focus-group methodology.

**Discussion:**

This study evaluates the Re-RAC intervention for older adults in RAC through a real-world pragmatic trial, examining activity performance, satisfaction, quality of life, well-being, and health outcomes for older adults in RAC facilities. The study also explores participant and staff experiences and evaluates cost-effectiveness. The results will offer valuable insights informing the future implementation and assessment of reablement interventions in RAC settings.

**Trial registration:**

ClinicalTrials.gov, ID: NCT06793501. Registered on 20 January 2025.

## Administrative information

Note: the numbers in curly brackets in this protocol refer to SPIRIT checklist item numbers. The order of the items has been modified to group similar items (see http://www.equator-network.org/reporting-guidelines/spirit-2013-statement-defining-standard-protocol-items-for-clinical-trials/).

## Introduction

### Background and rationale {6a}

The proportion of older adults is growing globally [1, 2]. This demographic shift presents significant challenges in sustaining good health and providing adequate social care for older adults and the number of individuals living in residential aged care (RAC) facilities is also expected to increase [1–3]. Both the World Health Organization (WHO) [4] and national regulations, such as Sweden’s [5], affirm that older adults have the right to live a dignified life while maintaining healthy habits, and to experience active aging and well-being. Care for older adults must strive to achieve these objectives. In contrast to these intentions, studies have shown that living in RAC facilities often has a passivating effect [6–8], indicating a need for interventions to address this issue.

In Swedish RAC facilities (e.g., long-term care facilities or nursing homes), residents typically have their own apartments and share common areas. Staff are available around the clock, primarily managing household duties. RAC facilities often provide group activities and opportunities for residents to move around within the building, fostering interaction in shared spaces (e.g., during food preparation) or in outdoor areas [9]. However, despite this adapted and accessible environment, older adults living in RAC facilities often struggle to influence their daily lives, participate in activities, and act spontaneously to the same extent as before. Consequently, their personal priorities risk becoming secondary to staff routines [6], resulting in passivity.

This passivity can lead to negative health outcomes and diminished quality of life (QoL) [7, 8, 10–13]. Additionally, depressive symptoms, feelings of loneliness, and social withdrawal are common among older adults in RAC facilities [7, 14, 15].

Self-determination, autonomy, and a sense of freedom [16, 17], along with the ability to engage in or perform meaningful activities, are closely linked to high QoL [18]. However, institutional settings such as RAC facilities can negatively affect older adults’ perceptions of their QoL [10]. Therefore, it is essential to adopt approaches that counteract passivity and strive to maintain a daily life that includes actions for autonomy and opportunities to practice meaningful activities. Unfortunately, rehabilitation resources designed to enhance the performance of meaningful activities in RAC facilities are often limited, leading to inequitable access to rehabilitation services based on residents’ needs [19]. One approach with potential to promote a more active life in RAC facilities is reablement [20].

Reablement is an approach intended to enhance an individual’s physical and functional abilities, with the goal of increasing or maintaining their level of self-reliance in meaningful daily activities and reducing their reliance on long-term services [21]. The core principles of reablement are person-centeredness and multidisciplinarity. The approach involves an initial comprehensive assessment of activity performance, followed by regular reassessments and the development of a goal-oriented support plan tailored to each individual [21]. Reablement has been shown to significantly improve daily functioning, motivation, engagement, and progress toward a reduced dependence on others. Additionally, it has demonstrated positive effects on the caregiving skills and well-being of carers [22–24].

Previous research on reablement has primarily focused on older adults living in ordinary housing with the aim of extending individuals’ independence and decreasing their reliance on care [25–27]. However, a literature review of reablement in RAC facilities suggests that this approach may hold promise in RAC settings but needs further exploration and adaptation to this specific context [20]. Not least to also evaluate the potential benefits against the possible risks of participating in reablement for this population.

In Sweden, reablement interventions in RAC facilities have not previously been studied. To address this gap, our research group has developed a reablement intervention tailored to the Swedish context, referred to as Reablement in Residential Aged Care (Re-RAC). A feasibility study was conducted to assess the intervention and study procedures, demonstrating their practicality and applicability [28]. The evaluation revealed no significant harms, which was anticipated given that the program is designed to enhance functional ability through use of low-intensity, individualized activities adapted to each participant’s capacity. Nonetheless, potential risks that may include temporary fatigue, frustration, or reduced motivation require continued investigation and evaluation on a larger scale. Thus, further evaluation is necessary through a larger-scale study using a randomized controlled trial (RCT) design to establish its efficacy and generalizability.

### Objectives {7}

The Re-RAC research project will, in a pragmatic randomized controlled trial (PrRCT), examine whether the Re-RAC intervention impacts activity performance and satisfaction, participation, quality of life, and well-being, in older adults living in RAC facilities. Additionally, the project aims to evaluate the health-economic effects of the intervention and explore potential associations with the outcomes. A further aim is to describe the experiences of both the participating older adults and the RAC facility staff involved in Re-RAC.

### Trial design {8}

This study is a multi-center prospective PrRCT with two parallel arms that will evaluate the Re-RAC intervention compared with treatment as usual (TAU) using quantitative, qualitative, and health-economic methods. The flow diagram of the study is presented in Fig. 1.

**Fig. 1 Fig1:**
[figure not shown]
Re-RAC flowchart Abbreviations: RAC = residential aged care; Re-RAC = Reablement in RAC, TAU = treatment as usual * According to sample size calculation

The study will be conducted as a superiority trial, evaluating differences in treatment outcomes between the two groups, randomized in a 1:1 ratio. Additionally, an incremental cost–utility analysis will be performed to evaluate the cost-effectiveness of the intervention. Individual interviews analyzed using qualitative thematic analysis [29] will be conducted to explore the older adults’ experiences of the intervention, while analysis of focus-group interviews with staff will follow the methods described by Kreuger and Casey [30] and Dahlin-Ivanoff and Holmgren [31].

This protocol follows the Standard Protocol Items: Recommendations for Interventional Trials (SPIRIT) guidelines [32]. The study will be reported in several papers according to the Consolidated Standards of Reporting Trials (CONSORT) guidelines [33], the Consolidated Criteria for Reporting Qualitative Research (COREQ) [34], and the Consolidated Health Economic Evaluation Reporting Standards (CHEERS) [35].

## Methods: participants, interventions and outcomes

### Study setting {9}

In Sweden, older adults who require extensive care that cannot be provided in ordinary housing can apply for an apartment in an RAC facility. A social assistance officer assesses and approves allocation to a RAC facility.

This study will be conducted in six RAC facilities—Rynningeviken, Ängen, Kornellen, Jeremiasgården, and two facilities still being recruited—located in Örebro municipality with about 160,000 inhabitants in central Sweden. These RAC facilities consist of several wards, each specializing in one of two areas: somatic or dementia care. Each facility has a minimum of 56 single-room apartments, with eight to ten residents per ward. The number of wards with somatic specialization varies between two and eight. The facilities also have common areas for dining and social activities. The RAC facilities provide social care and healthcare around the clock and have access to occupational therapists (OT) and physiotherapists (PT) when needed. The OTs are stationed at each RAC facility, whereas the PTs are commonly stationed at a nearby primary healthcare center and make regular visits to the RAC facility.

### Eligibility criteria {10}

RAC facilities in the specific municipality having wards with somatic specialization are eligible for the research project. The RAC facilities should not be involved in other rehabilitation research projects at the time, and they should have a stable staffing situation.

The staff supporting the older adults in the Re-RAC intervention will include nursing assistants, registered nurses, PTs, and OTs. They must be regularly employed or, in the case of external employment, be regular consultants at the RAC facilities and have completed the Re-RAC training.

Older adults aged 65 years and above, residing in a somatic ward at a RAC facility where the study will be conducted and meeting the inclusion criteria, are eligible to participate in the study. The inclusion criteria require that the older adult must be able to engage in conversations in Swedish and be able to participate in both the assessments and the intervention. Persons having severe cognitive impairment (≤ 17) [36] according to Mini Mental State Examination—Swedish version (MMSE-SR; screening for cognitive function [37]) or being very severely frail or terminally ill according to the Clinical Frailty Scale (≥ 8) (CFS-9, Swedish version [38]) will be excluded. The psychometric features for the MMSE-SR and CFS-9 are reportedly good [36, 38].

Personnel, irrespective of profession, who have completed the Re-RAC training, have worked with the intervention with at least one participant, and are Swedish speaking are eligible to participate as staff informants in the focus-group interviews.

### Who will take informed consent? {26a}

The overall management of RAC facilities in the specific municipality will sign a funding agreement, obtained by the Principal Investigator (PI). A member of the research team will meet potential participants—older adults living in an RAC facility selected for the study—who will provide written informed consent prior to the eligibility screening. Staff members who wish to participate as informants in the focus group interviews will also provide written consent to the researcher.

Participants and staff informants will be informed that they, without giving any reason, can withdraw from participation in the study at any time.

As per our exclusion criteria, individuals who are assessed to lack the capacity to provide informed consent at the time of recruitment will not be eligible to participate in the study. The current study does not include provisions for participation via legally authorized representatives.

### Additional consent provisions for collection and use of participant data and biological specimens {26b}

Data on healthcare consumption, pharmaceutical prescriptions, adverse events (AE), and adherence to the intervention will be extracted from medical records and healthcare administration systems. In the consent form, participants will be requested to allow the extraction of such data.

This study does not involve the collection and storage of biological samples.

## Interventions

### Explanation for the choice of comparators {6b}

In this study, Re-RAC will be compared with standard treatment as usual (TAU). TAU was chosen as the comparator because this study will be conducted in a real-world context in which, for ethical reasons, we cannot withhold standard treatment from any participant. Instead, Re-RAC will be an add-on intervention to TAU. The intervention group will receive both TAU and the Re-RAC intervention for 8 weeks, while the control group will receive only TAU.

The control group will be offered the Re-RAC intervention 3 months after the intervention has ended.

### Intervention description {11a}

#### Treatment as usual

TAU comprises a general approach in which all activities that the older adult engages in during everyday life are considered rehabilitative. The staff are encouraged to motivate the older adult to do as much as possible independently, to prevent loss of function and maintain the ability to perform activities. This approach does not involve any new direction toward specific activities or formulated personal goals. It does not include any formulated goals or follow-up. Additionally, no specific support is offered to the nursing assistants on how to encourage the older adult or how to follow up on the extent to which the approach is applied.

#### The Intervention: Reablement in Residential Aged Care (Re-RAC)

The Re-RAC intervention is described according to the TIDieR checklist and guide [39]. The checklist is available from the corresponding author on request.

##### Theoretical foundation

Re-RAC is rooted in the concept of reablement [21], which, in the field of aged care, is frequently used to denote a goal-oriented approach aimed at promoting meaningful activity [12, 40]. To further address this in Re-RAC, the Canadian Model of Occupational Performance and Engagement (CMOP-E) has been applied as a theoretical framework, emphasizing that engagement in activities involves motivation and willingness, and is based on what the individual finds meaningful [41].

The implementation of reablement in this study is characterized by a comprehensive assessment of the older person’s everyday activities, both current and past. This is done through a person-centered interview using the Canadian Occupational Performance Measure (COPM) [42, 43]. The COPM is based on the assumptions described in the theoretical framework of CMOP-E [41]. Based on the assessment, the older adult selects a personal activity goal, which consists of an activity they consider meaningful and wish to improve. Through collaboration between the older adult and staff, a goal-oriented support plan is developed to achieve the goal. Nursing assistant staff support the older persons in performing defined training activities and receive supervision from rehabilitation staff. The support plan and progress toward the activity goal are evaluated through regular reassessments during a fixed intervention period of 8 weeks. Hence, RE-RAC is based on the reablement concept, with multiple visits and support delivered by an educated and coordinated interdisciplinary team [21].

##### Materials and procedures

The following materials will be distributed to the nursing assistants, registered nurses, OTs, and PTs working at the participating RAC facilities:
Educational material for a half-day training session on the Re-RAC intervention, including handouts of the presentation.All study materials that staff will use during the trial will be distributed and explained during the training session. These include a logbook for documenting intervention activities, instructions for using the accelerometers, the individual support plan template, and instructions for conducting team meetings.

All potential study participants will receive:
Written information about the study, the procedure for participation, potential risks, voluntariness, and data management, as well as a consent form.

All included study participants will receive:
An information sheet that can be distributed to the participants’ relatives; andData collection material (e.g., instruction for accelerometers).

All participants in the intervention group will receive:
A person-centered, goal-oriented support plan that includes their goal and a schedule outlining the activities for each week;If the training involves any assistive devices, these will be prescribed and introduced jointly by an OT or PT and the nursing assistants; andA logbook placed in each intervention participant’s apartment for staff to complete.

##### Preparatory training and support for staff before and during intervention

Before the start of the study, all staff at the included wards will participate in a half-day (3.5-h) training session covering both theory and practice. Topics will include reablement, gerontology, motivational strategies, and teamwork. Case scenarios based on person-centeredness, healthy aging, and previous research on reablement will be presented and discussed in smaller groups. The training will also provide information about the practical implementation of Re-RAC, including motivational strategies and empathetic engagement. A film featuring a voluntary participant in the feasibility study [28] will be used to illustrate the process, from the initial interview to the implementation of the goal-oriented support plan and teamwork, further clarifying the Re-RAC working method.

The rehabilitation staff at each participating RAC facility will also participate in an additional half-day (3.5-h) training session specifically focused on helping nursing assistants in the implementation of the support plan and conducting check-ups. Check-ups will be offered in weeks 3 and 6 by the OT to provide support to both the participants and the nursing assistants. These check-ups are intended to identify any necessary adjustments to the intervention’s content and to provide ongoing support to both the participant and the nursing assistants as they work through Re-RAC. An additional purpose of these check-ups is to help the nursing assistants maintain the participants’ motivation and engagement throughout the process.

During the intervention, regular team meetings (involving nursing assistants, nurses, and the OT) held every other week and ward meetings (including all ward staff and the ward manager) held every fourth week will be used to communicate information about the intervention and the specific activities for each participant. These forums will also provide opportunities for reflection and guidance among the staff. Additionally, the OT will offer individual oral and/or practical guidance to the nursing assistants as needed.

##### Implementation of the intervention.

The intervention begins with an interview using the COPM [42, 43]. A researcher conducts the interview with the ward’s OT as an observer. The OT is present to understand the goal-setting process, as they will supervise the nursing assistants during the intervention. The OT will also contribute expertise related to participation in everyday life when formulating a measurable and realistic goal, within the relevant time frame.

During the interview, the older adult is asked to describe their daily life, including its activities and their performance, considering both the present and the past. The interview focuses on identifying both what works well and the challenges faced in daily life. Subsequently, the participant identifies and ranks the five most meaningful activities in their daily life. The participant also rates their occupational performance (COPM-P) and satisfaction (COPM-S) for each activity on a scale from 1 to 10.

In the second part of the interview, the older adult formulates a meaningful and relevant activity-based, person-centered goal for the intervention, based on one of the five prioritized activities identified in the previous step. The goal activity should be something the participant wants to perform or participate in but currently finds challenging or impossible. It must also be meaningful, relevant, and important for the participant’s well-being and QoL [42, 43]. An example of such a goal might be dressing independently, with the final goal being broken into smaller tasks that the participant practices with the nursing assistants during the 8 weeks of the Re-RAC intervention. Other examples might be moving independently to visit a neighbor in a different ward or participating in a social activity.

A goal-oriented support plan with specific activities to achieve the goal is developed by the OT together with the participant. A nursing assistant such as the participant’s contact person at the RAC can also be involved depending on the needs of the participant. These activities may include the use of assistive devices, environmental adjustments, and modified activity behaviors, such as physical exercise or task-specific training. Multiple training activities may be included and are tailored to the individual’s daily capacity. The time allocated for each participant is customized based on their needs and the nature of the goal. The intensity of the intervention can range from 2 to 7 days per week, with training sessions occurring once or multiple times per day, and each session lasting up to a maximum of 30 min.

The intervention lasts 8 weeks. The OT introduces the nursing assistants, who will support the older adult during the intervention, to the person-centered goal and the planned activities in the support plan. The nursing assistants receive supervision on how to support the specific participant according to the previously described support plan for staff. The intervention aims for ongoing progress with an increasing level of difficulty. Thus, the nursing assistants can adjust the level of difficulty based on the participant’s progress in their occupational performance. Additionally, the OT, PT, or the participants can initiate adjustments to improve the performance.

After 8 weeks, the intervention concludes with a renewed COPM assessment [42, 43], during which the participant’s occupational performance and satisfaction with the performance, related to the person-centered goal, are evaluated.

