### Relevant concomitant care permitted or prohibited during the trial {11d}

RAC facilities included in the study must not concurrently participate in other rehabilitation-related research during the trial period. Re-RAC will be evaluated against TAU, which includes access to standard rehabilitation services when clinically indicated. Accordingly, participants in both the intervention and control groups may continue receiving ongoing rehabilitation programs—such as physiotherapy or occupational therapy—intended to maintain functional ability. These services will not be withdrawn or modified for control group participants and will proceed as per the conditions at the time of study inclusion. Adjustments will only be made if a new rehabilitation need arises that cannot be postponed.

Control group participants will set a goal but will not receive active support to achieve it during the trial period. Once this period concludes (after three months), the facility’s responsible occupational therapist will be informed, and the participant may then be offered Re-RAC outside the study framework.

For participants in the Re-RAC group, any existing rehabilitation services will be supplemented with actions outlined in the Re-RAC plan. Services in place at the time of inclusion may be modified if such adjustments better support the participant’s goal attainment during the intervention phase.

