## Data collection and management

### Plans for assessment and collection of outcomes {18a}

Following the eligibility screening, all participants will undergo the baseline assessment and wear an accelerometer for one week. The baseline assessment will be conducted using several questionnaires. To address potential challenges related to low vision and to reduce cognitive load, the questionnaires will be administered in an interview format. Additionally, the older adults will be advised to use their regular hearing and vision aids during all assessments, including MMSE-SR.

At the end of the intervention period, a follow-up assessment will be conducted, mirroring the baseline assessment. In conjunction with the follow-up, a proxy assessment of the older adults’ occupational performance (COPM-P) will be carried out by the OT at the RAC facility (Table 1).

To collect data on participants’ experiences, semi-structured individual interviews will be conducted with participants from the intervention group. Staff experiences will be collected through focus-group interviews after supporting at least one participant in the intervention.

Additionally, data on adherence, healthcare consumption, incidents, and medication use will be extracted from medical records and administrative systems for a period of 3 months before baseline and 3 months after the intervention concludes.

Any deviations from the study protocol or participant discontinuations will be documented.

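### The baseline COPM interview doubles as the first step of Re-RAC, and the text implies, without stating it, that the occupational therapist attends in that arm only; the self-rated primary outcome may therefore be elicited differently by arm.

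*Protocol article*

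**What the plan says.** All references are to the protocol article.

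- *Implementation of the intervention* treats the interview as part of the treatment: "The intervention begins with an interview using the COPM". On attendance: "A researcher conducts the interview with the ward’s OT as an observer". The reason given is that "The OT is present to understand the goal-setting process, as they will supervise the nursing assistants during the intervention". The OT also has an active part: "The OT will also contribute expertise related to participation in everyday life when formulating a measurable and realistic goal, within the relevant time frame".
- The same section sets the order. The participant first names and ranks five activities and rates performance and satisfaction for each. The goal comes next: "In the second part of the interview, the older adult formulates a meaningful and relevant activity-based, person-centered goal for the intervention". It is built on one of the five, not necessarily the first.
- *Table 1* places allocation in the enrolment column (w−1) and COPM at w0 and w9. *Concealment mechanism {16b}* has the envelope opened after consent and screening, with no mention of the baseline assessment.
- *Relevant concomitant care {11d}*: "Control group participants will set a goal but will not receive active support to achieve it during the trial period". When that period is over, the "responsible occupational therapist will be informed".
- *Plans for assessment {18a}* describes one baseline assessment for everyone, then: "At the end of the intervention period, a follow-up assessment will be conducted, mirroring the baseline assessment". At follow-up the facility OT gives a proxy COPM-P rating, not limited to one arm. The COPM entry under *Measures* repeats the proxy rating.
- On which activity is scored, *Primary outcome* refers to the prioritized activity and *Measures* to the one of highest priority. The end of *Implementation of the intervention* has the renewed COPM evaluate performance and satisfaction in relation to the goal.

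**The concern.** COPM-P is a self-rating of an activity that the participant chooses, given by someone who knows their allocation. Its change over 8 weeks depends on the training, on how improvable the chosen activity is, and on the circumstances in which the rating is given. Randomization balances the participants. It does not balance a measurement step that is carried out after allocation and differently by arm.

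Two routes to bias are open. First, the therapist who will supervise the intervention may be in the room for baseline ratings in one arm and not in the other. Second, if the scored item is the goal activity, a professional may have helped steer that choice towards what is realistic in the time frame in one arm only. The planned ANCOVA adjusts for the starting score and for center. Two activities with the same starting score can differ in how much they are able to improve, and the model has no term for that. Either route could produce a between-arm difference in COPM-P change without any effect of training.

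**Working it through.** **What the text supports about each arm**

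| Step | Re-RAC | Control |
|---|---|---|
| Allocation known before baseline COPM | Yes (Table 1: w−1, then w0) | Yes (same) |
| Who leads the interview | Researcher | Not stated |
| OT in the room at baseline | Yes, stated | Not stated; the reason given for attendance does not apply, and {11d} has the OT informed only afterwards |
| OT input to the goal | Yes, stated | Not stated; unlikely on the same grounds |
| OT in the room at w9 | Not stated | Not stated |
| OT proxy COPM-P at follow-up | Yes | Yes, on the face of {18a} |

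The last row fits poorly with {11d}. To give a proxy rating at the end of the 8 weeks, the OT must know which activity the control participant rated. On one reading of {11d}, the OT first learns of it later.

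**Does OT input reach the scored item?**

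- If the item is the activity ranked first (*Primary outcome*, *Measures*), ranking and ratings precede the goal step. OT input to the goal then does not change the scored item, and only OT presence during the ratings could matter.
- If the item is the goal activity (end of *Implementation of the intervention*), the goal step selects which of five already rated activities becomes the endpoint. OT input then bears directly on it.

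The article does not settle which applies.

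**Illustration of size**

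Inputs from *Sample size {14}*: target difference 0.9, SD of change 1.3, two-sided 5%, 80% power, 25% dropout, 43 per arm.

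The plan's own figure: a two-sample t-test needs 33.74, so 34 per arm; 34 × 1.25 = 42.5, so 43 per arm and 86 in total. The stated figure is reproduced, and it does not bear on this point.

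Evaluable per arm: 43 × 0.75 = 32.25, about 32.

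SE of the difference = 1.3 × √(2/32) = 0.325.

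With a procedural shift b and no training effect, the chance of a significant result is Φ(−1.96 + b/SE) + Φ(−1.96 − b/SE). The document gives no value for b, so the values below are assumptions.

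| Assumed b | Share of 0.9 | b/SE | Rejection rate |
|---|---|---|---|
| 0 | 0% | 0 | 5% |
| 0.2 | 22% | 0.615 | 9.4% |
| 0.3 | 33% | 0.923 | 15.2% |
| 0.4 | 44% | 1.231 | 23.4% |

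These rates show what a shift of that size would do. They are not evidence that one exists.

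**The case against.** A reader might infer that the protocol prescribes two elicitation procedures: Re-RAC goals screened by a professional for achievability, control goals not, and Re-RAC ratings given before the supervising therapist at both time points. The documents do not support this, for four reasons.

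- No section says who attends the control interview. {18a} gives one baseline assessment for all, and its proxy rating suggests some OT knowledge of the rated activity in both arms.
- {11d} does not say what the OT is told. It may be only that the control period is over and Re-RAC can be offered.
- Activities are ranked and rated before the goal is formulated, a researcher leads, and the OT is described as an observer. Under *Primary outcome* and *Measures*, the scored item is fixed before any OT input.
- OT attendance at w9 is nowhere stated. The sentence on mirroring the baseline does not mention attendees, and the reason given for attending the first interview would not apply.

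It can also be said that the bias figure is assumed, that a condensed article may leave attendance to the full protocol, and that changing procedure mid-trial has a cost.

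These points limit the claim but do not remove it. Attendance is not simply left out: the article describes it for one arm, with a reason that holds for that arm only, after allocation is known. Nothing states that the procedure is the same for controls. The order of the interview protects the endpoint only if the highest-priority activity is what is scored, and the article is inconsistent on that. It gives no protection against the effect of the OT's presence on the ratings.

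**Conclusion.** The concern holds in a limited form. Followed as written, the article most naturally leads to a baseline COPM interview that differs between arms in who is present, for a self-rated primary outcome with unblinded participants. This is implied by *Implementation of the intervention*, Table 1 and {11d} together, and is not stated. Any effect on which activity is scored depends on the goal activity being the endpoint. Presence of the OT at w9 is a possibility that the text leaves open.

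The size and even the direction of any bias are unknown. The 9% to 23% false-positive range rests on an assumed shift of 0.2 to 0.4 units in favor of Re-RAC, an SD of 1.3 and 32 evaluable participants per arm. The case for change rests on the procedure, not on those figures. It is worth acting on because the remedy is small. If the interview is in fact already identical in both arms, a clarifying sentence and reconciled sections would suffice.

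**What to change.** - Use one written COPM procedure for both arms. The researcher alone takes the ranking, the ratings and the goal at w0, and the ratings at w9.
- Ideally complete the w0 interview before the envelope is opened.
- Let the OT join only after these are recorded, for support planning in the Re-RAC arm. This is preferable to bringing the OT into control goal-setting, which would add professional input to an arm meant to receive no active support.
- Fix the scored activity by the same rule in both arms, at baseline, and use it wherever the endpoint is described.
- Reconcile *Implementation of the intervention* (attendance at the interview, and the activity evaluated at 8 weeks), {11d}, {18a} and the COPM entry under *Measures*. State what the OT is told about control participants and when, so that the proxy rating is possible.

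Cost: a small change to the order of the interview, with no new staff, visits or participants. Moving the envelope step would also change the timing of allocation in Table 1 and {16b}, which is a larger amendment; the rest of the fix does not depend on it. Recruitment began in October 2024 (*Trial status*), so participants assessed before and after the change should be identified in the data.
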